## Abstract

**Background:**

The prevalence of obesity among children and adolescents has become a critical global public health issue, particularly in China, with significant increases observed over the past few decades. Despite regular surveillance for overweight and obesity in the past decades, there have been no annual reports provided to parents, resulting in a significant underrecognition of this issue. Early intervention and enhanced family-based educational intervention are necessary to address this growing problem.

**Objective:**

This protocol aims to evaluate the effectiveness of an enhanced family-based educational intervention in reducing overweight and obesity among school-age children and adolescents.

**Methods:**

This study uses a stratified cluster randomized controlled trial design involving 40 schools from 4 cities in Guangdong Province, selected based on economic levels and overweight and obesity prevalence. Schools will be randomly assigned to intervention or control groups. The intervention group receives an enhanced family-based educational intervention on obesity prevention, including health reports and educational materials. The control group continues with regular practices, including routine physical examinations, general health education activities, and school-based physical activity programs. The intervention spans 9 months, followed by a 3-month follow-up. Data on BMI, waist circumference, and waist-to-height ratio are collected at baseline and after 12 months to assess the potential effectiveness of the intervention.

**Results:**

This trial was funded in January 2024 and registered in the Chinese Clinical Trial Registry on November 5, 2024. Recruitment was completed in December 2024, with 20 schools enrolled in each of the intervention and control groups. Baseline data collection was completed during the 2024 fall semester, and follow-up data collection continued through December 2025. Data analysis will start after completion of the 12-month assessments. The study findings are expected to be published in 2026.

**Conclusions:**

This study protocol addresses the urgent need for effective interventions to combat the increasing prevalence of childhood and adolescent obesity in Guangdong Province. Given the significant underrecognition of the need for consistent reporting to parents, the proposed enhanced family-based educational intervention aims to fill this gap by raising parental awareness and promoting healthier lifestyles among children and adolescents. If successful, this approach could significantly reduce the risk of overweight and obesity in Chinese populations, which account for approximately one-fifth of the world’s population. The findings will provide insights into the efficacy of family-centered interventions and underscore the importance of integrating routine parental reporting into existing surveillance programs.

## Introduction

The global prevalence of obesity among children and adolescents has increased nearly 10-fold over the past 4 decades, from 0.7% in 1975 to 5.6% in 2016 among girls and from 0.9% to 7.8% among boys in the same period [1,2]. This prevalence continues to rise, with more than 390 million children and adolescents aged 5 to 19 years being overweight, including 160 million who are living with obesity as of 2022 [3]. While the prevalence of obesity has plateaued at high levels in high-income countries, it is still accelerating in low- and middle-income countries, including China [2,4]. The mean prevalence of overweight and obesity among Chinese children and adolescents increased significantly from 5.3% in 1995 to 20.5% in 2014 [5], and more recent data reported by the latest round of China Chronic Disease and Nutrition Surveillance (2015-2019) indicated that the prevalence among children and adolescents aged 6 to 17 years was approximately 19% for overweight and obesity as of 2019 [6]. Childhood and adolescent obesity can affect both physical and psychological health [3], academic attainment, and quality of life [7,8]. In the longer term, it can also increase the risk of cardiometabolic diseases [9], musculoskeletal problems [10], and cancers in adulthood [11].

Despite the alarming rise in childhood and adolescent obesity, many Chinese parents and caregivers hold the belief that a chubby child is a sign of good health and nutrition, reflecting social and cultural factors where a fuller body is seen as a sign of prosperity and well-being [12]. This perception is compounded by the common belief that children who are overweight will naturally shed the excess weight as they grow older [13]. However, without proper intervention, children who are overweight are more likely to become adults who are overweight or obese, carrying the associated health risks into later life [14,15]. The issue is further complicated by the misconception that obesity primarily affects adults, leading to insufficient attention to the dietary and physical activity needs for children and adolescents [16,17]. Many parents are not fully aware of the serious health risks linked to childhood and adolescent obesity, such as diabetes, hypertension, and psychological issues [18-20]. This lack of awareness contributes to a lack of urgency in addressing and managing weight issues among young people [19,20].

Existing literature underscores the need for early intervention to curb the trajectory of obesity from childhood into adulthood [15,20,21]. Studies have shown that interventions targeting children and adolescents can effectively reduce BMI and improve motor skills [22-24].

Despite regular surveillance and monitoring of overweight and obesity in China, there has been a significant underrecognition of these issues due to the absence of consistent reporting to parents. Furthermore, evidence suggests that interventions with significant family involvement achieve better outcomes in reducing childhood and adolescent obesity [25]. However, the effectiveness of enhanced family-based educational interventions aimed at children and adolescents with overweight or obesity has not yet been fully evaluated. Notably, most studies evaluating obesity interventions in China have not adequately measured the degree of family involvement during implementation [26-32]. Furthermore, these studies were confined to single, high-income cities, such as Shanghai [31], Nanjing [28,32], Guangzhou [30], and Beijing [29], raising concerns about their generalizability to broader, more diverse populations across the country. Therefore, these gaps highlight the need for enhanced family-based educational interventions to raise awareness and promote healthier lifestyles among children and adolescents, together with their families.

This study aims to evaluate the effectiveness of enhanced family-based educational interventions in reducing the prevalence of overweight and obesity among school-aged children and adolescents in Guangdong Province. By integrating routine parental reporting into existing surveillance programs and providing comprehensive family-centered interventions, this study seeks to address the critical gaps in awareness and management of childhood and adolescent overweight and obesity. The findings will contribute valuable insights into effective strategies for obesity prevention and control, ultimately improving the health outcomes for children and adolescents in China.

## Methods

### Study Design

This study will use a multistage cluster randomized controlled trial (RCT) design. All cities in Guangdong Province will be divided into 2 economic strata. The 2 cities with the highest prevalence of overweight or obesity will be selected from each stratum. Schools within these cities will be randomly assigned to either the intervention group or the control group. The intervention group will receive enhanced family-based educational interventions, while the control group will continue with regular practices. The study will involve baseline data collection, 4 rounds of interventions, and follow-up assessments over 12 months. Figure 1 shows the flowchart of the study design.

**Figure 1. F1:**
[figure not shown]
Overview of the study design. KAP: knowledge, attitude, and practice.

### Setting

The study will be conducted in Guangdong Province, which includes 21 prefecture-level cities. Within these cities, a total of 40 schools (including primary, middle, and high schools) will be selected based on their participation in an initiative called Surveillance for Common Disease and Health Risk Factors Among Students in Guangdong Province. The selected schools will represent a diverse socioeconomic and demographic student population to ensure the generalizability of the study findings. The intervention will be implemented in both urban and rural settings to capture the varying dynamics of childhood and adolescent obesity across different environments.

### Stratification, Randomization, and Allocation Concealment

Stratified randomization will be used, considering the comparability between the intervention and control groups. First, all cities in Guangdong Province will be divided into 2 economic strata. The 2 cities with the highest prevalence of overweight or obesity will be selected from each stratum. Second, schools will be stratified according to school types, with 4 primary schools, 4 middle schools, and 2 high schools being selected in each city. Subsequently, the selected schools within each stratum will be randomly assigned in a 1:1 ratio to either the intervention or control group. To ensure rigorous allocation concealment, a random allocation sequence will be generated by an independent statistician blinded to the participating schools. Opaque, sealed envelopes containing group assignments will be prepared by staff not involved in intervention implementation, and allocations will be disclosed only after completion of school enrollment.

### Inclusion and Exclusion Criteria

Participants in this study will be school-aged children and adolescents from Guangdong Province who meet the following criteria: aged between 8 and 17 years and enrolled in grades 4 and 5 (primary school), grades 7 and 8 (middle school), and grades 10 and 11 (high school). They must be identified as overweight or obese based on the Screening for Overweight and Obesity Among School-Age Children and Adolescents (WS/T 586‐2018) standards during the baseline assessment. Additionally, both students and their parents or guardians must provide informed consent to participate in the study.

Participants will be excluded if they meet any of the following criteria: refusal by students or their parents or guardians to participate in the study; presence of mental health conditions, intellectual disabilities, or other factors that may impede understanding or cooperation with the study procedures; and presence of severe illnesses or undergoing major medical treatments, such as dialysis or chemotherapy, which may affect the study outcomes.

### Sample Size

Assuming an effect size (Cohen *d*) of 0.1, an SD of 0.05, a significance level (α) of .05, and a power (1-*β*) of .9, with an intracluster correlation coefficient of 0.01, an average cluster size (*m*) of 160 students, and an overweight and obesity prevalence rate of 20%, the required sample size *n* for each cluster (school) was calculated using the following Cohen *d* formula:

(1)
$$n={\left(\frac{z_{1-\frac{a}{2}}+z_{1-\beta }}{d}\right)}^{2}\times 2\times {\left(SD\right)}^{2}$$

Considering that the sample size for a cluster RCT needs to be adjusted based on the intracluster correlation coefficient, the adjusted sample size n was calculated. By multiplying the adjusted sample size *n* by the number of clusters (schools), the total sample size was estimated to be 539 students. Accounting for a 20% dropout rate, the total sample size required is approximately 674 students.

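### The sample-size formula combines a Cohen d with an SD² term and counts a per-arm n once per school, so 539 students and 90% power do not follow from the stated assumptions

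*Protocol article*

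**What the plan says.** The Sample Size section of the protocol article opens "Assuming an effect size (Cohen *d*) of 0.1, an SD of 0.05", with "a significance level (α) of .05" and a power "of .9, with an intracluster correlation coefficient of 0.01". It adds an average cluster size of "160 students, and an overweight and obesity prevalence rate of 20" percent. The printed formula is the square of (z for 1−α/2 plus z for 1−β) divided by d, times 2, times SD². The section calls this a Cohen d formula and describes the result as the number required in each school. It then adjusts for the intracluster correlation and states that, multiplied "by the number of clusters (schools), the total sample size was estimated to be 539 students". A 20% dropout allowance raises this to 674.

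Three facts from other sections bear on the calculation. Setting gives 40 schools. The randomisation section gives 1:1 allocation. Inclusion and Exclusion Criteria limits participants by weight status: "They must be identified as overweight or obese". Study Outcomes names two primary outcomes, the 12-month changes in BMI and in zBMI. The Sample Size section does not say which of them the 0.1 and 0.05 describe.

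**The concern.** Three steps in the calculation do not fit together.

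- **Scale.** A Cohen d is a mean difference already divided by the SD. The formula divides by d and then multiplies by SD² as well, so the SD is counted twice. With SD = 0.05 this lowers n.
- **Unit.** The factor 2 makes this the two-sample formula, whose result is a number per arm. The section assigns it to a school and multiplies by the number of schools. This raises n.
- **Cluster size.** The design effect appears to use all 160 sampled students per school, although only those with overweight or obesity are analysed. This also raises n.

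Because the errors run in opposite directions, the final total looks plausible. What is at stake is the meaning of the 90% power claim. If the trial finds no difference, a reader who relies on that claim could take the result as good evidence against an effect of 0.1 SD. Strengths and Limitations mentions short follow-up as a reason an effect might be missed, but not sample size.

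**Working it through.** **Inputs.** From Sample Size: d = 0.1, SD = 0.05, two-sided α = 0.05, power 0.90, ICC = 0.01, m = 160, prevalence 20%, dropout 20%. From Setting: 40 schools. The z values are 1.960 + 1.2816 = 3.2415.

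**1. Reproducing the published total.**
- n = (3.2415/0.1)² × 2 × 0.05² = 1,050.7 × 2 × 0.0025 = 5.25
- Design effect = 1 + (160 − 1) × 0.01 = 2.59
- 5.25 × 2.59 × 40 = 544. With n taken as 5.2, 5.2 × 2.59 × 40 = 538.7, which rounds to 539.
- 539/0.8 = 673.75, which rounds to 674.

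The rounding to 5.2 is inferred, but the route is the one the text describes. A one-sided α (444), m = 32 (275), 20 clusters (272), 2 arms (27) and n rounded up to 6 (622) all miss 539.

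**2. Size and direction of each error, if d is standardised.**
- SD² term: the base n should be 2 × (3.2415/0.1)² = 2,101 per arm. 2,101/5.25 = 400, so n is 400-fold too small.
- 40 schools instead of 2 arms: 40/2 = 20, so the total is inflated 20-fold.
- m = 160 instead of 160 × 0.20 = 32: the design effect is 2.59 instead of 1 + 31 × 0.01 = 1.31, a further inflation. The plan's own total implies only 539/40 = 13.5 students per school.

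**3. Power at d = 0.1 with 40 schools.** Effective N = N/[1 + (N/40 − 1) × 0.01]; SE = √(4/effective N); power = Φ(0.1/SE − 1.96); effect detectable with 90% power = 3.2415 × SE.

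| Analysed N | Per school | Design effect | Effective N | SE | Power at 0.1 SD | Effect at 90% power |
|---|---|---|---|---|---|---|
| 539 | 13.5 | 1.125 | 479 | 0.0914 | 19% | 0.30 SD |
| 674 | 16.9 | 1.159 | 582 | 0.0829 | 23% | 0.27 SD |
| 1,024 | 25.6 | 1.246 | 822 | 0.0698 | 30% | 0.23 SD |
| 1,280 | 32 | 1.31 | 977 | 0.0640 | 35% | 0.21 SD |

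Here 1,280 = 40 × 32 is every eligible student, and 1,024 = 1,280 × 0.8 is that number after 20% dropout. For 539 analysed, other design effects give 21% (no clustering), 17% (1.31) and 11% (the plan's own 2.59). A t reference on 38 degrees of freedom gives 18.6% instead of 19.3%.

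**4. Whether more students per school could reach 90%.** Before clustering, 4 × (3.2415/0.1)² = 4,203 students are needed in total. With 40 schools, effective N cannot exceed 40/0.01 = 4,000 however many students each school supplies. So 90% power at d = 0.1 is unreachable with 40 schools at this ICC.

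**5. The raw-difference reading.** If 0.1 is a difference in outcome units with SD 0.05, the standardised effect is 0.1/0.05 = 2. The formula then gives 5.25 per arm, or 5.25 × 2.59 × 2 = 27 in total with the plan's own design effect. On that reading 539 students give essentially 100% power.

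**The case against.** The strongest reply is that the printed formula, with its SD² term, is the standard one for a raw mean difference, so that only the Cohen d label is wrong. On that reading power is not low at all. This part stands: a reader might infer from the arithmetic that the trial simply has 19% power, and the document does not support that without the condition that 0.1 is standardised. It does not rescue the paragraph, however. The section applies the Cohen d label both to the 0.1 and to the formula. The raw reading implies a 2-SD effect, and 539 is then about 20 times what the formula asks for.

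A second reply is that 539 is a planned minimum after dropout. The article reports 20 schools enrolled per arm but no number of students, so the analysed number may be larger. This also stands, and it is why the power is shown over a range. Even with every eligible student analysed, power at 0.1 SD is about 35%.

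A third caution concerns the remedy. Applying the corrected formula with 32 per school gives 4,203 × 1.31 = 5,506 students, and a reader might conclude that this number would restore 90% power. It would do so only in about 5,506/32 = 172 schools. Spread over 40 schools it means 138 per school, a design effect of 2.37 and about 67% power.

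Finally, that m = 160 means all sampled students is an inference. The stated 20% prevalence and the eligibility rule make it likely. The power figures in the table do not depend on it, because they use the analysed number per school.

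**Conclusion.** The calculation is wrong as written and should be corrected before the 12-month analysis. The SD² term makes the base n 400-fold too small for a standardised d. The multiplication by schools and the cluster size of 160 both push the total up, so it would be wrong to say that all three errors cause low power.

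If d = 0.1 is standardised, as the text labels it, 539 analysed students in 40 schools give about 19% power (11% to 21% across design effects), and no cluster size reaches 90%. If 0.1 is a raw difference, power is about 100%, but the label and the total are still wrong. The firm conclusion is therefore that 539 and 90% power at a Cohen d of 0.1 do not go together and that the scale of the effect is undefined. The low-power figures rest on the document's own label, its ICC of 0.01, equal school sizes and a normal approximation.

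**What to change.** Before the 12-month analysis, replace the paragraph as follows.

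- Name the primary outcome (change in BMI or in zBMI) and the scale that 0.1 and 0.05 refer to.
- If d is standardised, remove SD² and use n per arm = 2 × (z₁₋α/₂ + z₁₋β)²/d² × [1 + (m − 1) × ICC]. If 0.1 is raw, keep the SD term, remove the Cohen d label and justify an effect of 2 SD.
- Treat n as per arm, do not multiply it by the number of schools, and set m to the analysed students with overweight or obesity per school.
- Check the result against the 40 schools enrolled, because the formula alone does not show that 90% power at 0.1 SD is unreachable with that number.
- Keep the 40 schools, withdraw the claim of 90% power at d = 0.1, and state the effect detectable with 90% power for the actual numbers: about 0.30 SD with 539 analysed, 0.27 SD with 674 or 0.23 SD with 1,024.

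The cost is one corrected paragraph and, on the standardised reading, a less favourable power statement. Recruitment is complete, so this is a reporting correction. It needs no extra participants and does not change the intervention.

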### Intervention and Control

The intervention group will receive an enhanced family-based educational intervention in addition to the regular prevention measures implemented by schools. Each student and their parents will receive 1 health report (Multimedia Appendix 1) and 4 sets of educational materials, which will be developed by the Guangdong Provincial Center for Disease Control and Prevention and delivered by schools. Each set includes an enhanced health education booklet, a family weight management action guideline, and an advocacy letter (Multimedia Appendix 2). Details of these intervention components are shown in Table 1. Participants in the control group will only receive the regular prevention measures implemented by their schools. These measures may include routine physical examinations, general health education activities, and school-based physical activity programs, but no additional educational materials or personalized health reports will be provided to the control group.

**Table 1. T1:** Description of the enhanced family-based educational intervention components.

Intervention component	When it was delivered	What was delivered
Health report	Within 1 month of the baseline survey (ie, the first round of the intervention)	Information on the student's height, weight, waist circumference, BMI, and their overweight or obesity status
Advocacy letter	Within 1 month of the baseline survey (ie, the first round of the intervention), and at 3, 6, and 9 months after the first intervention	Information on the impact of being overweight and obese on the physical and brain development of students and the “Three 1/2s” initiative: increasing the daily intake of fresh fruits and vegetables by half, reducing the daily intake of sugary drinks and fried foods by half, and increasing daily outdoor physical activity duration by half
Enhanced health education booklet	Within 1 month of the baseline survey (ie, the first round of the intervention), and at 3, 6, and 9 months after the first intervention	Information on the short-term and long-term health risks associated with childhood and adolescent overweight and obesity, healthy dietary habits to prevent obesity, physical activity recommendations, BMI calculation methods, and screening standards for childhood and adolescent overweight and obesity
Family weight management action guideline	Within 1 month of the baseline survey (ie, the first round of the intervention), and at 3, 6, and 9 months after the first intervention	Details of the implementation of the “Three 1/2s” initiative, methods for monitoring children and adolescents' growth, and monthly checklists for tracking adherence to the intervention

### Study Outcomes

Primary outcomes are the changes in BMI and standardized BMI (zBMI) over a 12-month period. These outcomes will provide a direct measure of the intervention’s effectiveness in reducing overweight and obesity among the participants. The change in BMI will be assessed from baseline to the end of the study, while the change in zBMI will account for age and sex differences, offering a more nuanced understanding of the weight status changes in the school-aged children and adolescents.

Secondary outcomes include the incidence and recovery rates of both general and central obesity; changes in standardized waist-to-height ratio (zWHtR) and standardized waist circumference (zWC); and changes in parental knowledge, attitude, and practice (KAP) scores (Multimedia Appendix 3) [33]. Specifically, the incidence of general obesity will be determined by newly diagnosed students with obesity at the end of the study among participants who are not obese at baseline, and the recovery rate will be calculated based on the number of students who transition from obesity to nonobesity status. Similarly, the incidence and recovery rates of central obesity will be assessed. Additional secondary outcomes involve changes in zWHtR and zWC over 12 months. The staff who measure the children’s weight and height will be blinded to the school allocation. Furthermore, KAP scores will be assessed at the start of the intervention and at 3, 6, 9, and 12 months after the intervention to gauge improvements in health literacy regarding childhood and adolescent overweight and obesity. These comprehensive outcomes will help elucidate the effectiveness of the enhanced family-based educational interventions and their impact on health behaviors and literacy.

Process evaluation will be used to evaluate the feasibility and acceptability of the trial by assessing parental compliance. Specifically, parent questionnaires (Multimedia Appendix 4) are administered at 3, 6, 9, and 12 months after the intervention to evaluate adherence to dietary and physical activity recommendations.

